## Methods/design

### Aims

The primary aims are to strengthen protective factors and promote childhood life changes for 7–14 year-olds who are relatives of people with addiction problems, and to contribute to the support that Swedish society gives to these children. We want to break the pattern of alcohol and drug problems being transmitted between generations. This entails a preventive intervention targeted at those who have an increased risk of developing addiction problems and other problems that are consequences of their situation. A secondary aim at the universal level is to promote protective factors among children of the same ages, and to prevent the development of drug addiction among children.

In order to increase our chances of achieving these goals, we are implementing the project as a collaboration between practitioners and researchers. Our goals also include increasing the relevance of the project, developing knowledge, and improving practical implementation. This can also provide an increased opportunity to disseminate experiences to other groups, and for other activities, after the method has been tested and evaluated based in the Swedish context and in three priority areas – social services, a NGO, and schools.

The research covers five research questions:How can participants in the implementation of the program be recruited?How can leaders be supported to enable the implementation of a high-quality program?What is the significance of the program for children’s development and mental health?Does the program work differently for different groups in relation to gender, social background, place of residence and age?Does the intervention work differently at a universal, selective or indicative level?

The research questions will be studied through an implementation evaluation, using self-assessment forms, interviews and observations using an established “checklist”, as well as through an impact assessment, which has a randomized, controlled pre-post design, in which self-reports, interviews and adult reports of testing instruments are used. Our main target group consists of children aged 7 to 12 years who are in one of the organization’s schools, social services or the value-based organization IOGT-NTO Junior Federation, Junis. A secondary target group consists of the deliverers.

### Intervention method

The method of the present project, developed by experts in Europe, concerns giving children their own self-empowerment, strengthening protective factors, and, in the long run, their resilience. In Sweden, the material has been named “I want, I can, I dare”.

The methodology that will be further developed and evaluated in this project is called RESCUR (the resilience curriculum) aimed at increasing children’s resilience, i.e., children’s ability to cope with crises, changes and stressors without falling apart. The method is rooted in research on human resilience [1, 2].

It has been found that, when implementing foreign methods in a new country or culture, they rarely work [44], which provides the backdrop to this European cooperation. Instead of incorporating an American method, which in many cases has failed in Sweden [45–48], the starting point was to develop a method suited for European conditions (see https://www.rescur.eu). The present project mainly uses the leader’s/teacher’s guide developed for the target age group, i.e., children aged 7 to 12 years. In addition, there is a handbook for parents so that they can strengthen the work of promoting child protection factors at home and interact with the school in advancing child development. There is also a special common introduction in the material describing the theoretical foundation of the method. When these guides were written, all partners were aware that a particular focus would be on children in risk situations [2]. The guides describe very clearly how work with the children is going to be conducted, and there is a resource package with, for example, music, pictures, mindfulness exercises (recorded) to facilitate the implementation of the method. Instructions for teachers of children in three different age groups (4–5, 6–8 and 9–12 years) and guides for teachers and parents have been developed in seven different languages ​​(English, Greek, Italian, Croatian, Maltese, Portuguese and Swedish) [https://www.rescur.eu].

The curriculum is based on the following six themes, where each theme is divided into sub-themes. Clear goals are described for all exercises, which are the basis of the practical implementation of the method.Developing communication skills: effective communication, and assertiveness.Establishing and maintaining healthy relationships: healthy relationships, and cooperative skills, empathy and moral reasoning.Developing a growth mindset: positive and optimistic thinking, and positive emotions.Developing self-determination: problem solving, and empowerment and autonomyBuilding on strengths: positive self-concept and self-esteem, and using strengths in academic and social engagementTurning challenges into opportunities: dealing with adversity and setbacks, dealing with rejection, dealing with loss, dealing with family conflict, dealing with bullying, and dealing with change and transition.

The exercises are divided into three optional levels of difficulty (basic, intermediate and advanced level) to ensure that the exercises suit the target group and its needs.

Each RESCUR class begins with a brief mindfulness exercise. RESCUR has been piloted and evaluated in six countries with good results, and then further developed on the basis of lessons learned. The teachers who worked on the method with their students have been very satisfied, especially with the mindfulness part (mindfulness has been shown in a meta-analysis to be an effective, preventive method for children in the school environment) [49].

Due to the extensive material developed in RESCUR, we have chosen to constrain the part being evaluated. This evaluation will focus on themes 1, 5 and 6. The exercises are also divided into three optional levels of difficulty (basic, intermediate and advanced level) to ensure that the exercises fit the particular group you work with. Since RESCUR is a new method, being implemented at the same time as the evaluation takes place, and for comparable results, the intervention groups under investigation will only work at basic level.

The method is theoretically promising and builds on principles of successful preventive and promotional work, but it has never been tested or researched in Sweden. We believe it can be an important element in the support offered to children, and their relatives and teacher/group leaders. However, it should be stressed that it is not a way of replacing actions at the structural level carried out by municipalities or county councils; successful promotive and preventive work needs to be implemented on many levels and by many different actors. RESCUR is a method to complement other efforts made by society in to provide children and relatives with improved protective tools so that they, in case of difficult situations, can not only handle the situation but also be strengthened. In other words, it is about helping children to get as good life chances as they possibly can.

The RESCUR program has a training component for the teachers and group leaders who will implement the curriculum. The training lasts 3 days. First, there is a two-day introduction to the theory and methodology of RESCUR, which also includes practical exercises. The teachers and group leaders are supervised through a monitoring visit to the different sites every sixth month for RESCUR in Sweden. The supervisors also observe the implementation and document results on an implementation checklist. There is also a one-day educational session for follow-up.

### Research design and methodology

The project has been divided into three phases. The first phase involved planning and conducting a preliminary study, including the application to the research ethics committee (first year). We started the project, formed a project team and appointed a project manager, worked on the manuals to make them more user-friendly, gave information about and marketed the project among organizations and policy-makers, recruited participants for the evaluation, finalized the project and research plan, including all measuring instruments. The Ethical Review Board approved the research project (EPN dnr 2016/460).

The project is based on close collaboration between Junis and the research group, with a clear division of work and responsibility. The purpose of Junis’s activities is to provide health promotion for children aged 7–15 years in an encouraging environment where the child’s self-esteem and self-confidence grow together with secure and safe adults. The organization will be responsible for planning and implementing the program in all groups. The research group is responsible for the scientific study of implementation and effects of the program for the participants in groups and school classes who are part of the intervention and control groups. The research consists in a randomized, controlled, longitudinal survey of the RESCUR program. This means taking baseline measurements before the intervention begins, and follow-ups at 6 months, 1 year, and then 2 years.

The second phase involves implementing the program “I want, I can, I dare” (RESCUR) in Junis’s group activities, in groups throughout social services and in school classes in different municipalities and across the country (i.e., in different residential areas). The third phase involves analysis and reporting on the project’s implementation and its effects.

### Design

The project will be carefully evaluated from two perspectives: implementation and impact. In order for a theoretically promising method to work at all, the method must have been implemented effectively and correctly. Inadequate implementation leads to poor or no results for what would otherwise have been an effective method. We will study the implementation through both self-assessment forms, reported by group leaders when the program has been used for half a year, and observations made according to a formalized checklist. Implementation of the method is fundamental to properly evaluating the effects of the method, which is the second part of the evaluation of the project. At the same time, we are also interested in directly studying the extent to which it is possible to implement the method as intended. This is one of the research issues in the project.

The effects of the method on protective factors and resilience will be measured using a randomized, controlled pre-post follow-up design with two types of groups. We will study the effects both statistically and with regard to practical relevance [62]. We will use our waiting list to create a control condition. In this way, we can use the principle of giving everyone who so wishes have the chance of receiving the intervention in combination with increasing its internal validity. The waiting list group is initiated 1 year after baseline measurements have been taken. We take a pre-measurement before the intervention begins among the participants (even adult reports will be collected), and then take measurements after one semester, 1 year, and 2 years (Table 1). Adult reports will be collected at baseline and at the measurement after 1 year. On other occasions, only the children’s self-reports will be collected. By collecting data from two different informants for each child, we ensure that we get information on each child to facilitate analysis of data reliability. In addition, we will probably get a “truer” picture of the child’s behavior.

**Table 1 Tab1:**
[figure not shown]
Schedule of enrolment, interventions, and assessments

The controlled study has three different arms. In the case of schools, we cluster-randomized participants to one of two conditions: (A) intervention schools or (B) waiting list or control schools. Randomization has been done at school level. Thereafter, the baseline measurements were performed in both conditions, and, after that, the intervention group began its activities, and measurements were taken as described above (Table 1). One year after the baseline measurement intervention group (A), the waiting list group began its program. Measurements are finally to be made a year later.

In the case of Junis’s groups, it was not feasible to do a cluster randomization at the managerial level as the involvement of local chapters was more difficult to achieve. The groups will be led by regular Junis volunteers.

As for the social services group, we will have the same arrangement, but no waiting-list control condition. Here, a new round of groups is planned for the second year. On the other hand, we will have a follow-up measurement of the first wave’s intervention groups in year 3 for both the Junis and the social services groups. The groups will be run by social workers.

However, it will be possible to compare developments in these two study arms with the data collected in the control schools.

### Participants and recruitment

A calculation of statistical power has been made for the interventions. For the universal intervention, there is an effect size of d = 0.3 and a power of 0.8, and the corresponding statistics are expected to test a group size of 176 in each group. The recruitment of schools for the evaluation of RESCUR has been completed. These schools have been recruited from different parts of Sweden, and in both urban and rural areas. There are 8 intervention schools in five municipalities, including 10 classes in school year 1, and 8 classes in school year 4. The intervention group includes 394 children. There are 9 school in the waiting list control schools in six municipalities, including 10 classes in school year 1, and 9 classes in school year 4. The waiting list controls include 401 children. The number of classes in which RESCUR is carried out in the municipalities is larger than necessary to carry out the project based on an evaluation or “power perspective”. Oversampling, however, is a common and good strategy to deal with any delays, etc. from the project, and thus to reduce threats to the implementation of the project. Participants are randomized to the intervention and waiting list/ control groups based on residence and school. The planned survey is regarded as having adequate statistical strength.

The project group has trained 23 teachers in the intervention schools. In March 2018, 20 teachers in the waiting list control schools will be trained in the RESCUR intervention.

A power analysis for the interventions in social services and the NGO has been performed. For the selective groups, an effect size of d = 0.5 and power of 0.8 is calculated, which results in a double-sided statistical testing of group differences (alpha = 0.05), and a group size of 64 children in each of the two groups. The planned size allows for a certain amount of dropout in the study.

Recruitment for the evaluation of RESCUR in the social services groups is ongoing. At present, several social-services units have expressed an interest in being included in the evaluation. We will recruit participants to 8 groups with approximately eight participants for the first year. Here, there will be no randomization, but a second round of groups is scheduled for the second year. It provides a total of 128 children over the 2 years. The planned size of the sample in social services is less, since previous research has clearly shown that interventions in targeted or selected groups have a significantly higher effect size than those in universal groups (i.e., the school). The age of participants in the social services groups will be 7–9 and 9–12 years. During 2017, RESCUR groups have started in social services in five municipalities, including 42 children. Fifteen group leaders from six municipalities have received the RESCUR training so far.

For groups within Junis, 22 leaders from ten different districts have been asked to participate. We plan to have a total of 16 groups of approximately 8 participants in the Junis group. It provides 128 participants. The age of the participants will be between 7 and 12 years. Eight Junis leaders from 5 municipalities have been trained, but so far only one group has started to use the RESCUR intervention.

An important question to answer in the project is how the recruitment of participating actors as well as children is facilitated in the three types of organization. Another important question is whether the RESCUR method works equally well for children in the three types of organizations.

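### The school power calculation (176 per group) assumes individually randomised children although schools were randomised, so its stated power does not apply and the adequacy statements are unsupported

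*Protocol article*

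**What the plan says.** In the protocol article, the Design section (text following Table 1) describes the school part as a cluster trial: "In the case of schools, we cluster-randomized participants to one of two conditions", and "Randomization has been done at school level".

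The section Participants and recruitment gives the calculation: "For the universal intervention, there is an effect size of d = 0.3 and a power of 0.8", from which "the corresponding statistics are expected to test a group size of 176 in each group". No intraclass correlation (ICC), school size or design effect accompanies it. Significance level and sidedness are given only for the selective groups ("double-sided statistical testing of group differences (alpha = 0.05").

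The same section reports completed recruitment: "There are 8 intervention schools in five municipalities, including 10 classes in school year 1, and 8 classes in school year 4", with 394 children, and "There are 9 school in the waiting list control schools in six municipalities", with 401 children. It describes the number of classes as more than power requires, presents the surplus as protection against delays and similar problems, and concludes: "The planned survey is regarded as having adequate statistical strength".

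**The concern.** Children in one school tend to resemble each other. When schools are allocated, the variance of the treatment difference is inflated by roughly 1 + (m − 1) × ICC, where m is the number of children per school, and the test has degrees of freedom set by the number of schools. A group size derived for independent children leaves out both. The only power benchmark given for the school comparison is 176, so the claims of surplus and adequacy rest on a figure for a different design.

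The school comparison is the only randomised evidence in the programme, and its controls also serve as comparator for the Junis and social services groups. A reader who takes the power to be at least 0.8 could give a null result more weight as evidence of no effect at d = 0.3 than the design supports.

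**Working it through.** **Inputs from the article.** d = 0.3; power 0.8; 8 schools with 394 children (m₁ = 394/8 = 49.25); 9 schools with 401 children (m₂ = 401/9 = 44.56); overall mean 795/17 = 46.8 per school.

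**Assumptions.** Two-sided alpha of 0.05 for the school comparison (stated only for the selective groups). ICC ρ from 0.01 to 0.10, since none is given. Baseline correlation r = 0 or 0.5 at both child and school level, since none is given. No attrition unless noted.

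**Step 1: reproduce 176.** Normal formula: n = 2 × (1.960 + 0.842)² / 0.3² = 174.4, so 175 per group. The exact two-sample t-test needs 175.4, so 176, as stated. A one-sided test would need 138, so two-sided 0.05 was used. The selective-group figure of 64 at d = 0.5 follows in the same way (63.8). The design effect inside 176 is therefore 1.

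**Step 2: the cluster formula.**

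SE² = (1 − r²) × { [1 + (m₁ − 1)ρ]/n₁ + [1 + (m₂ − 1)ρ]/n₂ }

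Power is the probability that a noncentral t variable with 8 + 9 − 2 = 15 df and noncentrality 0.3/SE exceeds 2.131 in absolute value.

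Example, ρ = 0.02, r = 0: the design effects are 1 + 48.25 × 0.02 = 1.965 and 1 + 43.56 × 0.02 = 1.871. SE = √(1.965/394 + 1.871/401) = 0.0983, noncentrality 0.3/0.0983 = 3.05, power 0.81.

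**Step 3: the recruited sample, 394 versus 401.** MDE is the effect detectable with 80% power.

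| ICC | Power at d = 0.3, unadjusted | MDE, unadjusted | Power at d = 0.3, r = 0.5 | MDE, r = 0.5 |
|---|---|---|---|---|
| 0.01 | 0.91 | 0.257 | 0.97 | 0.222 |
| 0.02 | 0.81 | 0.295 | 0.91 | 0.255 |
| 0.03 | 0.73 | 0.328 | 0.84 | 0.284 |
| 0.05 | 0.59 | 0.386 | 0.71 | 0.334 |
| 0.10 | 0.39 | 0.503 | 0.49 | 0.436 |

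If the children are treated as independent, the same sample has power of about 0.99.

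**Step 4: break-even ICC.** Power equals 0.80 at ρ = 0.022 unadjusted and 0.036 with r = 0.5. A normal approximation in place of 15 df gives 0.028 and 0.044. If 80% of children are retained (assumed), the 15-df values become 0.016 and 0.031.

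**Step 5: the stated 176 per group in the same 17 schools, unadjusted.** With 15 df, power is 0.67, 0.61 and 0.46 at ρ = 0.01, 0.02 and 0.05. The normal approximation gives 0.73, 0.66 and 0.51. It is below the stated 0.80 either way.

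Class-level clustering within schools and unequal school sizes were not modelled. Unequal sizes would lower power further.

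**The case against.** The strongest reply is that the trial recruited 394 and 401 children, not 176 per group. A reader might infer from the missing design effect that the trial is underpowered and that the surplus claim is false. The article does not support that. At an ICC of 0.01 or 0.02 the recruited sample still has unadjusted power of 0.91 or 0.81, and in that range the adequacy statement holds.

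The reply goes further. Data management and analysis plans latent change models and effect sizes that account for the initial level, so unadjusted figures are pessimistic. The break-even ICC rises from 0.022 to 0.036 at r = 0.5, and to 0.046 at r = 0.6 or 0.063 at r = 0.7. This part stands, and it is why the adequacy statements should be called unsupported rather than wrong. No value of r is given either, however, so the adjustment cannot be counted on to rescue the claim: at ICC 0.05 and r = 0.5 power is 0.71.

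A condensed article may also leave an ICC to the full protocol. That does not help here, because 176 reproduces exactly with no design effect and so cannot already contain one. Nor was the surplus presented as an allowance for clustering; the article offers it as cover for delays and similar problems.

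Finally, the arithmetic behind 176 is correct for its own formula. The fault is that the formula does not match the design.

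**Conclusion.** The point holds in this form. The group size of 176 belongs to an individually randomised trial, so the stated power of 0.8 is not a property of the school-randomised design; in these 17 schools 176 per group gives about 0.46 to 0.67 for ICCs from 0.05 down to 0.01. The statements on surplus classes and adequate strength have no valid calculation behind them. They are true or false according to an ICC that the article does not give: for the recruited sample they fail above about 0.022 unadjusted, or about 0.036 with an assumed baseline correlation of 0.5, on 15 df and with no attrition. The result rests on those assumptions and on a two-sided 5% test. It does not show that the trial is underpowered, and it says nothing about whether the eventual analysis will model clustering, which is a separate matter.

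**What to change.** In Participants and recruitment, replace the power statement for the universal intervention with a cluster-randomised calculation for the schools actually recruited: 8 and 9 schools, 394 and 401 children, mean school size about 47, 15 df, a justified ICC range, and the planned baseline adjustment with its assumed correlation. Report the resulting power at d = 0.3 and the minimum detectable effect, with and without an allowance for attrition. Make the statements on surplus classes and adequate statistical strength conditional on the ICC.

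The change is to wording only. School recruitment is complete and no new schools are needed; allocation, sample and analysis are unaffected. The cost is a stated power that is less favourable than the present text implies.
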